### Sample size

In calculating the sample size, a power of 90% and an α value of 5% were assumed, to detect a mean change in pain intensity, measured on the 100 mm visual analogue scale, of 32.3 mm between the initial and final values among the experimental group, and a mean reduction of 19.8 mm among the control group (standard deviation 31.9 mm), on the basis of the results of a pilot experiment carried out beforehand at the Pain Treatment Unit at the Dos Hermanas Healthcare Clinic between April and December 2006. These assumptions require a sample size of 140 patients per group, in a design with two equal groups. We propose to recruit 400 patients in order to allow for a 30% drop out rate.

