#### Statistical analysis

A comparison will be made of the baseline variables for each of the groups, to test the homogeneity obtained from the random allocation to groups, in terms of differences of the means and of proportions. The magnitude of the difference in the possible imbalance produced by the random allocation between the two groups will be quantified in terms of ratios of the means and of proportions (using that of the placebo group as a reference level), and the final adjustment will be made by secondary analyses with multiple linear regression models.

In the unadjusted analysis, significance tests will be performed for comparison among k samples (parametric or otherwise, depending on whether or not the distribution of the outcome variables is asymmetric, and on the homogeneity of their variances), taking that of the placebo group as a reference level, and using comparison tests for differences of the means in the primary outcome measure (pain intensity on the 100 mm VAS), both for the inter-group comparisons (for independent samples) and for comparisons between the initial and final levels in each group (in this case, using tests for non-independent or paired samples).

Linear regression models will be constructed for the primary outcome measure, adjusted by the baseline level and using ITT analysis. The group variables will be included, taking that of the placebo group as a reference level, together with the results recorded by the medical professionals, and the sociodemographic data (age and sex), and the baseline levels for the variables related to the severity of the process (pain intensity and frequency). Adjustments will be made for possible confounders, using criteria of statistical significance and of confusion. The detection of possible interactions with the treatment group variable will be evaluated using criteria of statistical significance for the corresponding interaction terms. The level of statistical significance will be set at α < 0.05. The model will be reconstructed, removing the observations with Cook's distances exceeding the 90^th ^percentile of the distribution, in order to test the consistency of the results.

An economic analysis will also be carried out, from the standpoint of the interests of the Andalusian Public Health System.

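### The plan does not fix which analysis of week-9 VAS is primary, and both candidate analyses leave choices to the trial data

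*Protocol article*

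**What the plan says.** All of this is in the Statistical analysis section of the protocol article unless noted.

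- **Baseline comparison and adjustment.** The first paragraph opens: "A comparison will be made of the baseline variables for each of the groups, to test the homogeneity obtained from the random allocation to groups". Imbalance is to be quantified as ratios of means and proportions, and "the final adjustment will be made by secondary analyses with multiple linear regression models".
- **Unadjusted test.** The second paragraph compares the groups on the 100 mm VAS with tests that are "parametric or otherwise, depending on whether or not the distribution of the outcome variables is asymmetric, and on the homogeneity of their variances". The same sentence refers to comparing differences of means.
- **Regression.** The third paragraph builds ITT linear regression models for the primary outcome, adjusted for baseline level, with group, age, sex and baseline severity among the terms. It adds: "Adjustments will be made for possible confounders, using criteria of statistical significance and of confusion". Interactions with treatment are judged by significance.
- **Error level.** One statement covers everything: "The level of statistical significance will be set at α < 0.05".
- **Analysis set.** The Discussion bases the principal outcome on ITT and adds a per-protocol analysis.
- **Sizing.** The Sample size section compares mean changes in two groups: "a power of 90% and an α value of 5% were assumed".

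**The concern.** A confirmatory trial needs one result that decides the primary question. Here there are two candidates. The first paragraph's label points to the unadjusted test. The third paragraph points to the regression, because it attaches both the primary outcome and the ITT principle to it.

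Neither reading yields a fully specified analysis. The unadjusted test may turn out to be a comparison of means or a rank test, depending on the observed distribution and variances. A rank test does not estimate the mean difference on which the trial was sized. The regression's covariates depend on significance and on how they shift the estimate. Under randomisation, baseline imbalance arises by chance, so testing for it is a poor guide to what to adjust for.

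At stake is what the trial reports if the two routes fall on opposite sides of 0.05. The plan does not settle this, so the choice could be made after the results are seen.

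**Working it through.** **1. Reproduce the sample size.** The inputs, from the Sample size section, are expected VAS changes of 32.3 mm with true treatment and 19.8 mm with placebo, so the difference is 32.3 − 19.8 = 12.5 mm, with SD 31.9 mm, two-sided 5% and power 90%.

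n per group = 2 × (1.960 + 1.282)² × (31.9 / 12.5)² = 136.9, rounded up to 137. The exact t-test gives 138. The plan's 140 agrees, and 280 / 0.70 = 400. A one-sided test would need 112, so the plan was sized two-sided, on one comparison of two means.

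**2. Each route alone under no effect.** The plan gives no selection thresholds or correlation, so these are assumptions: 4,000 simulated trials, 140 per arm, normal outcomes, correlation about 0.5, six candidate covariates, a covariate kept if p < 0.05 or if it moves the group coefficient by more than 10%. Monte Carlo SE is 0.34 percentage points.

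| Rule | Type I error |
|---|---|
| Unadjusted test, t or rank chosen by observed skewness and variance | 5.3% |
| Regression with data-selected covariates | 5.3% |
| Fixed baseline-adjusted model | 5.2% |
| Either of the first two may count | 8.2% |

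The last row lies below the 1 − 0.95² = 9.75% that applies to independent tests, because the two results are correlated.

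**3. Dependence on the correlation.** Take the simplest pair: a change-score test and a fixed baseline-adjusted model (ANCOVA). Assume that 31.9 mm is the SD of the change and that baseline and follow-up have equal variance σ² and correlation ρ. Then:

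- variance of change = 2σ²(1 − ρ), and ANCOVA residual variance = σ²(1 − ρ²)
- the ratio of ANCOVA to change-score variance is (1 + ρ)/2
- the two test statistics have correlation √[(1 + ρ)/2]
- change-score noncentrality = 12.5 / (31.9 × √(2/140)) = 12.5 / 3.813 = 3.28
- ANCOVA noncentrality = 3.28 / √[(1 + ρ)/2]
- power = Φ(noncentrality − 1.96)

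The either-significant and disagreement columns come from the bivariate normal distribution of the two statistics.

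| ρ (assumed) | √[(1+ρ)/2] | Either significant, no effect | Power, change score | ANCOVA noncentrality | Power, ANCOVA | Verdicts disagree at 12.5 mm |
|---|---|---|---|---|---|---|
| 0.3 | 0.806 | 7.8% | 90.6% | 4.07 | 98.2% | 8.1% |
| 0.5 | 0.866 | 7.3% | 90.6% | 3.79 | 96.6% | 7.0% |
| 0.7 | 0.922 | 6.8% | 90.6% | 3.56 | 94.5% | 5.4% |

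Simulation of this pair gives about 6.3% to 8.1% for either significant and roughly 6% to 8% for disagreement, consistent with the table.

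**The case against.** **A hierarchy can partly be read from the text.** Regression adjustment is called secondary, the trial is sized on an unadjusted comparison of mean change, and the sentence on test choice mentions differences of means. This has weight: the problem is an ambiguity, not complete silence. It is not conclusive, because the third paragraph gives the primary outcome and ITT to the regression. Even if the unadjusted test is primary, its form still depends on the data.

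**A statistical analysis plan may exist, and this is a condensed article.** Selection thresholds and a full covariate list could fairly be left to it, and their absence is not the point. The point concerns rules that the article states, which a later plan would have to overrule.

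**The unadjusted test is valid and has its planned power.** This stands. The gain from baseline adjustment is a benefit of the fix, not a defect in the plan.

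A reader might also infer more than the document supports:

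- *That choosing the test or the covariates from the data itself inflates the error.* In the simulation each stays at about 5.3%. The excess comes from having two eligible results.
- *That the t-test and the rank test are two separate chances of success.* The plan picks one by rule.
- *That a formal normality pre-test is planned.* Only asymmetry and homogeneity of variance are mentioned.
- *That significant interactions stay in the primary model.* The text says they are evaluated, not that they are retained.
- *That per protocol is a further rival for the primary result.* The Discussion already bases the principal outcome on ITT.

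**Conclusion.** The point holds as an undesignated primary analysis, with data-dependent choices inside both candidates. It does not hold as a claim that those choices alone break the 5% level.

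If either result may count, type I error is about 6% to 8% instead of 5%. At the planned effect, about 6% to 8% of trials would give conflicting verdicts with no rule to resolve them. Both ranges rest on 140 analysed per arm and an assumed correlation of 0.7 to 0.3. The simulation that includes selection also assumes six candidate covariates and a 10% threshold. The document supplies none of these assumed values, so the figures show the scale of the problem and are not estimates for this trial.

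The inflation is modest, but the trial's main conclusion depends on the choice left open. The sample size calculation itself is sound.

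**What to change.** Before allocation is unblinded, reword the Statistical analysis section as follows.

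1. **Name one primary analysis:** an ITT linear model of week-9 VAS on treatment, with baseline VAS and therapist as covariates. Therapist is the randomisation stratum. Fix any further covariates, such as age and sex, in advance, and use no data-driven selection.
2. **Replace the test-choice rule** with robust standard errors, which allow for unequal variances and, at this sample size, tolerate skewness. The estimate remains a mean difference in mm, the quantity on which the trial was sized.
3. **Label the rest.** The unadjusted test, covariate-selected models and interaction tests become secondary or sensitivity analyses.
4. **Report baseline comparisons descriptively** and do not let them drive adjustment.

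This needs no extra data, and the sample size stays at 140 per group and 400 recruited. Under the assumed correlations and equal variances, power rises from about 90% to 94–98%. The cost is the rewording and a few degrees of freedom for therapist: 15 − 1 = 14, out of about 280 analysed patients.

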We have designed this randomised controlled multicentre study to investigate the effectiveness and safety of sensory stimulation via auricular implants in patients with UCR, treated by healthcare professionals (15 doctors and nurses) at 10 healthcare clinics in the Sevilla-Sur Healthcare District (within the Andalusian Public Health System). The primary specific goal is to assess effectiveness in terms of the lessened pain intensity, measured on a visual analogue scale (VAS), experienced by patients with UCR, at 9 weeks after beginning treatment. As secondary specific goals, we intend to: a) evaluate the effectiveness in terms of lessened pain intensity, measured on the VAS, at 6 months after beginning treatment; b) evaluate the effectiveness in terms of improvement recorded on the Spanish version of the McGill Pain Questionnaire (MPQ-SV), at 9 weeks and at 6 months after beginning treatment; c) evaluate the effectiveness in terms of patient-perceived improvement (PPI) at the end of the treatment; d) evaluate the impact on time lost off work due to sickness; e) evaluate the credibility of the technique and patients' expectations, as well as its relation to the results; f) evaluate the effectiveness in terms of reduced consumption of analgesic and anti-inflammatory medication; g) evaluate the effectiveness in terms of improved health-related quality of life (SF-12); h) compare the effectiveness of the technique with regard to the healthcare professionals' degree of training and practice; i) compare the characteristics of the Lattinen test and the MPQ-SV; j) analyze the cost-effectiveness of treatment with auricular pressure for patients with UCR.

This study is funded by the *Instituto de Salud Carlos III*, *Fondo de Investigaciones Sanitarias *(File No. PI0790058) and by the Health Ministry of the Andalusian Regional Government (File No. 00462007).

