### Randomization and treatment allocation

Sampling will be by consecutive selection in accordance with the inclusion-exclusion criteria, for a period of 12 months until the sample is complete. The randomized allocation to each of the two branches of the study will be carried out using specialized computer software (Epidat v. 3.1), at the Research Unit of the Costa del Sol Hospital (Málaga, Spain), in a 1:1 plan (true auricular pressure: placebo) in blocks of 6, stratified by therapist. Neither the clinics nor the healthcare professional participating in the study will be involved in the randomization process, and the randomization sequence will remain concealed until the end of the study. Patients who meet the criteria for inclusion and who sign their informed consent will be included in the study. After inclusion in the study, the healthcare professional will call the randomization clinic at which the patient is registered, and will be informed, both by phone and by fax, which of the two study branches the patient has been assigned to. This procedure ensures that the randomization process is not influenced by the healthcare personnel participating in the study. The success of the blinding of the patients will be evaluated at the end of the treatment period.

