### Treatment

The 15 healthcare professionals who will participate in the study (doctors and nurses) have taken a training course in auricular pressure techniques for the treatment of UCR, with a total of 15 hours' theory and 15 hours' practical content. Of these 15 professionals, 5 had also received specific training in acupuncture and related techniques, with an average of 320 hours theoretical training and over 100 hours' clinical practice with these techniques. All the patients will be allowed to use symptomatic medication for pain relief in case of need.

The patients in both groups will be called 8 times for treatment (once a week) for the auricular implants to be inserted.

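### Therapist is the randomisation stratum but is not named in the primary model; the cost is small and conservative, and the training comparison (goal h) needs a model with therapist variation

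*Protocol article*

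**What the plan says.** **Allocation.** Under Randomization and treatment allocation, patients are assigned 1:1 "in blocks of 6, stratified by therapist". Subjects gives 15 doctors and nurses at 10 centres. The Discussion describes the stratification differently, as a way of giving every clinic equal proportions of the two arms.

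**Primary model.** Statistical analysis states: "Linear regression models will be constructed for the primary outcome measure, adjusted by the baseline level and using ITT analysis". The named terms are treatment group, the results that the professionals record, age, sex, and baseline pain intensity and frequency. Further confounders may enter on significance or confounding criteria, and interactions with group are judged by significance. Neither therapist nor clinic is named.

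**Goal h.** One secondary goal in the Background is to "compare the effectiveness of the technique with regard to the healthcare professionals", by their degree of training and practice. Treatment gives the split: "Of these 15 professionals, 5 had also received specific training in acupuncture and related techniques". The article assigns no analysis to this goal.

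**The concern.** A factor used to balance the arms should normally be in the analysis. If outcomes differ between therapists, stratification removes that variation from the treatment contrast, while a model without therapist leaves it in the residual. The reported SE is then larger than the true one and some power is lost.

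The confounder rule does not repair this. A factor balanced by design hardly moves the treatment estimate, so a confounding criterion would tend to leave it out. A significance criterion would make its entry depend on the data. The term for results recorded by the professionals most naturally means therapist-recorded data such as the Lattinen test, not therapist identity.

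For goal h the exposure belongs to the therapist. Evidence on it comes from 5 versus 10 therapists, however many patients each one treats. An analysis that counts patients as independent could overstate that evidence.

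**Working it through.** **1. The plan's own figure.** Sample size: "a power of 90% and an α value of 5% were assumed". The mean changes are 32.3 and 19.8 mm (difference 12.5 mm) and the SD is 31.9 mm. The two-sided normal approximation gives

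n = 2 × [31.9 × (1.960 + 1.282) / 12.5]² = 137 per group.

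The t-based version gives 138, and a one-sided test would give 112. The stated 140 therefore reproduces as two-sided, with power 0.906 at 140. Allowing for dropout, 280 / 0.70 = 400, as stated.

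**2. Main effect without a therapist term.** The naive SE is 31.9 × √(2/140) = 3.81 mm. Three assumptions follow, none given in the article: a share ICC of the variance lies between therapists, the arms are balanced within therapist, and the treatment effect is the same for all therapists. Then:

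- true SE = 3.81 × √(1 − ICC)
- actual type I error = 2 × [1 − Φ(1.96 × naive SE / true SE)]
- power without therapist = Φ[(12.5 − 1.96 × naive SE) / true SE]
- power with therapist = Φ(12.5 / true SE − 1.96)

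| ICC | True SE (mm) | Naive SE too wide by | Type I error | Power without | Power with | n per group with therapist |
|---|---|---|---|---|---|---|
| 0 | 3.81 | 0% | 0.050 | 0.906 | 0.906 | 137 |
| 0.01 | 3.79 | 0.5% | 0.049 | 0.907 | 0.909 | 136 |
| 0.02 | 3.77 | 1.0% | 0.048 | 0.909 | 0.912 | 135 |
| 0.05 | 3.72 | 2.6% | 0.044 | 0.912 | 0.920 | 131 |
| 0.10 | 3.62 | 5.4% | 0.039 | 0.918 | 0.933 | 124 |

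A simulation (15 therapists × 18 patients, 4,000 runs) at ICC 0.05 rejected 4.3% of the time without therapist and 4.9% with it as a fixed effect.

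**3. Goal h as a plain comparison of patients by training.** There are 280 / 15 = 18.7 evaluable patients per therapist if recruitment is even, so about 93.3 versus 186.7 patients. The naive SE is 31.9 × √(1/93.3 + 1/186.7) = 4.04 mm. The true SE is the naive SE × √[1 + (18.7 − 1) × ICC].

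| ICC | True SE (mm) | Type I error |
|---|---|---|
| 0.01 | 4.39 | 0.071 |
| 0.02 | 4.70 | 0.092 |
| 0.05 | 5.55 | 0.153 |
| 0.10 | 6.73 | 0.239 |

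Simulation gave 0.147 at ICC 0.05 and 0.242 at ICC 0.10.

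**4. Goal h as a treatment-by-training interaction.** The naive SE is 31.9 × √[4 × (1/93.3 + 1/186.7)] = 8.09 mm. With therapist intercepts only, at ICC 0.05, the true SE is 8.09 × √0.95 = 7.88 mm. The naive SE is then too wide (type I error 0.044).

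Now let the treatment effect vary between therapists with SD τ. The patient-level residual variance is 31.9² × (1 − ICC) − τ²/4. The interaction variance is 4 × (residual variance) × (1/93.3 + 1/186.7) + τ² × (1/5 + 1/10). At ICC 0.05:

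- τ = 5 mm: true SE 8.32 mm, type I error 0.057
- τ = 8 mm: true SE 8.96 mm, type I error 0.077

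**5. The same variation in the main effect.** For inference to therapists in general, the main-effect variance is (residual variance) × 2/140 + τ²/15. At ICC 0.05 the true SE is 3.92 mm (τ = 5) or 4.23 mm (τ = 8), against the naive 3.81 mm. The naive SE is then too narrow.

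**The case against.** **The list of terms is not closed, and this is an article.** A full analysis plan may name therapist. What stands is that the article does state a covariate set for the primary model, that the stratification factor is not in it, and that the route for adding covariates would tend to pass over a balanced factor.

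**The main-effect cost is minor and safe.** This stands. With a common treatment effect the test is conservative, power stays above the planned 90%, and no primary conclusion is threatened.

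**A reader might infer that the plan makes the main-effect SE too wide and the training-level SE too narrow.** The article does not support this as a fact. It gives no variance components, and at ICC 0 neither error arises. It also states no model for goal h, so there is no specified SE to call too narrow. If goal h is tested as an interaction, therapist intercepts alone make that SE too wide. It becomes too narrow only when the effect varies enough between therapists, and the same variation can make the main-effect SE too narrow for inference to therapists in general. Both directions hold together for a plain comparison by training with a common treatment effect, which the article does not say it will use.

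**A reader might also infer that a non-significant interaction would be taken as proof that the 30-hour course is enough.** Nothing in the article says so. Its aim is to evaluate treatment by professionals trained on that course, not to show that training levels are equivalent.

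**The two accounts of stratification may be compatible.** If each therapist works at one clinic, balance within therapist also gives balance within clinic. The article does not say this, so the text still needs reconciling.

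**Conclusion.** The concern holds in a limited form. Therapist defines the randomisation strata and is neither named in the primary model nor guaranteed to enter it. For an assumed ICC of 0.01 to 0.10 and a similar treatment effect across therapists, the SE is 0.5% to 5.4% too wide and the type I error is 0.049 to 0.039. Naming therapist moves power from about 0.91–0.92 to 0.91–0.93. The 140 per group and the 400 recruited are unaffected.

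For goal h the point is a caution about an analysis not yet described. A plain patient-level comparison would have a type I error of about 0.07 to 0.24 over the same ICC range. An interaction test would reach about 0.06 to 0.08 only if the effect varies between therapists (SD 5 to 8 mm, ICC 0.05). All these figures assume even recruitment per therapist and balance within therapist, which incomplete blocks and dropout will only approximate.

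**What to change.** 1. In Statistical analysis, name therapist as a prespecified term in the primary model, as 15 fixed levels or a random intercept, outside the confounder-selection rule.
2. Reconcile Randomization and treatment allocation (strata are therapists) with the Discussion (balance by clinic), and say how therapists are nested in clinics.
3. For goal h, specify a mixed model with a random therapist intercept and a random treatment slope by therapist. Test training by treatment on therapist-level degrees of freedom (about 15 − 2 = 13), and report the estimate with its interval as exploratory.

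The cost is analysis wording only. Allocation is by therapist, so therapist is already known for every patient. The downside is a wider interval for goal h.

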### Results measures

Each patient will fill in a self-response questionnaire before beginning the treatment (T0), at one week after ending treatment (T1) and after six months (T2). This questionnaire will include one-dimensional data (100 mm visual analogue scale) and multidimensional data (McGill Pain Questionnaire, Spanish version [30]) on rachialgia, medication currently being taken and health-related quality of life (SF-12), together with information on days off work due to rachialgia. Additionally, before beginning treatment, the patients will be asked to fill in a form on sociodemographic questions. Any adverse effects of the study techniques, and any use of rescue medication by the patient will also be recorded. During the initial evaluation, an anamnesis will be obtained on the characteristics of the rachialgia, and note will be taken of the duration of the pain. In each treatment session, the therapist will record the five pain-related variables that constitute the Lattinen test (LT), which is widely used in pain treatment clinics in Spain [31]. These variables are: pain intensity, pain frequency, consumption of analgesics, level of activity, and nocturnal hours' sleep. Each item is scored on a Likert scale from 0 to 4; thus, the sum of the five variables may range from 0 to 20 points, with higher scores reflecting greater pain severity. In addition, the auricular points selected for each patient will be recorded (Table 1).

**Table 1 T1:** Data collection schedule. Measurement times and variables used in the study.

Visit No.	T0	Weekly treatment								T1	T2
Week No.	0	1	2	3	4	5	6	7	8	9	24
Data provided by the patient											
Pain intensity (VAS 100 mm)	X									X	X
Multidimensional pain evaluation (MPQ-SV)	X									X	X
Quality of life (SF-12)	X									X	X
Analgesics and antiinflammatory drugs prescribed	X									X	X
Sociodemographic variables	X										
Credibility and expectations				X							
Improvement perceived by the patient										X	
Assessment of blinding effectiveness										X	
Data provided by the therapist											
Multidimensional pain evaluation (LT)	X	X	X	X	X	X	X	X	X	X	X
Auricular points used		X	X	X	X	X	X	X	X	X	
Adverse events		X	X	X	X	X	X	X	X	X	
Economic evaluation											
Direct and indirect costs: healthcare professionals and patients	X									X	X

VAS 100 mm: Visual analogue scale (0–100 mm); MPQ-SV: McGill Pain Questionnaire, Spanish version; LT: Lattinen test

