#### Secondary outcome measures

▪ Changes in pain intensity, measured on the 100 mm VAS, at 6 months after beginning treatment.

▪ Changes in the McGill Pain Questionnaire (MPQ), at the end of treatment and after 6 months. The MPQ pain evaluation index consists of 64 pain descriptors divided into 19 subclasses. Within each subclass, the descriptors are classified by intensity.

▪ Satisfaction on the improvement perceived by the patient (PPI) [33], scored by the patient on a 7-point Likert scale as follows: 1 = extremely satisfied; 2 = very satisfied; 3 = moderately satisfied; 4 = no strong feelings either way; 5 = somewhat unsatisfied; 6 = very unsatisfied; 7 = extremely unsatisfied.

▪ Changes in health-related quality of life, according to the Spanish version of the 12-item Short Form health survey, Version 2, at the end of treatment and after 6 months. This questionnaire is of a generic type, derived from SF-36, which has been validated for use in Spain [34], and which enables the quantification of quality of life in 8 dimensions (physical function, physical role, pain, general health, vitality, social function, emotional role, mental health) and expresses two summary components (physical and mental).

▪ Changes in the results of the Lattinen test and in the consumption of analgesics and NSAIDs (whether or not prescribed by the GP), at the time of randomization, after each treatment session, at the end of treatment and after 6 months.

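### The regression for the 9-week VAS takes in therapist-recorded results with no time limit; read literally, it adjusts the ITT effect for post-randomisation outcomes

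*Protocol article*

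**What the plan says.** The Statistical analysis section of the Protocol article states: "Linear regression models will be constructed for the primary outcome measure, adjusted by the baseline level and using ITT analysis". The group variable then enters with placebo as reference, "together with the results recorded by the medical professionals, and the sociodemographic data (age and sex", and after these comes a separate item, "the baseline levels for the variables related to the severity of the process (pain intensity and frequency". The therapist-recorded results carry no time point; the severity variables are expressly baseline values.

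What the therapist records is set out under Results measures: "In each treatment session, the therapist will record the five pain-related variables that constitute the Lattinen test (LT". The five items are "pain intensity, pain frequency, consumption of analgesics, level of activity, and nocturnal hours' sleep". Table 1 lists three kinds of data provided by the therapist:

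- the Lattinen test, at T0, each weekly session, T1 and T2;
- the auricular points used, from week 1 to T1;
- adverse events, from week 1 to T1.

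Secondary outcome measures lists change in the Lattinen test as an outcome, measured "at the time of randomization, after each treatment session, at the end of treatment and after 6 months". Under Randomization and treatment allocation, the treating professional "will be informed, both by phone and by fax, which of the two study branches the patient has been assigned to".

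The Statistical analysis section also plans an unadjusted between-group test on the VAS. Of chance imbalance at baseline it says "the final adjustment will be made by secondary analyses with multiple linear regression models".

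**The concern.** A regression that is meant to deliver an ITT effect should condition only on variables fixed before allocation. Apart from the T0 Lattinen score, every therapist-provided item in Table 1 arises after it. The Lattinen score is the most troublesome, because it measures much the same thing as the VAS (pain intensity is one of its items) and the trial itself expects treatment to change it. At T1 it is taken at the same visit as the primary VAS.

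A model containing that score asks whether the arms differ in VAS among patients with equal on-treatment or end-of-treatment pain. That is not the ITT question. If treatment works on both scales, part of the benefit is credited to the covariate and the treatment coefficient shrinks. Because the therapist knows the arm, the covariate can also carry assessment bias into the coefficient.

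**Working it through.** **1. The plan's own figure.** Inputs from Sample size: mean changes of 32.3 and 19.8 mm, so a difference of 12.5 mm; SD 31.9 mm; α 5%; power 90%. Two-sided, per group:

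n = 2 × [31.9 × (1.960 + 1.282) / 12.5]² = 136.9, so 137 (138 with the t distribution), against 140 stated. With 30% dropout, 280 / 0.70 = 400, as stated. The calculation reproduces. It is a comparison of two mean changes with no covariates, and at 140 per group its power is about 90.6%.

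**2. Effect of adding a post-randomisation score M.** With δ_Y and δ_M the treatment effects on the outcome and on M, and r their within-arm correlation, the adjusted coefficient is expected to be

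β = δ_Y − r × (SD_Y / SD_M) × δ_M.

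The planned standardised VAS effect is 12.5 / 31.9 = 0.39 SD. If M shifts by a fraction f of that amount in its own SD units, this simplifies to β = 12.5 × (1 − r × f) mm.

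The standard error is approximately 31.9 × √(1 − r²) × √(2/140) × √(1 + (0.39 f)² / 4), and power is Φ(β / SE − 1.96).

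Example with r = 0.5, f = 1: β = 12.5 × 0.5 = 6.25 mm; SE = 31.9 × 0.866 × 0.1195 × 1.019 = 3.36; power = Φ(1.86 − 1.96), about 46%.

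**3. Results.** Both r and f are assumptions; the documents give neither.

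| Shift in M (f) | r = 0.3 | r = 0.5 | r = 0.7 |
|---|---|---|---|
| Same as VAS (1) | 8.75 mm, 66% | 6.25 mm, 46% | 3.75 mm, 27% |
| Half (0.5) | 10.6 mm, 83% | 9.4 mm, 81% | 8.1 mm, 84% |
| None (0) | 12.5 mm | 12.5 mm | 12.5 mm |

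The share of the effect removed is r × f: 30%, 50% and 70% in the first row, and 15%, 25% and 35% in the second. With no shift there is no bias, and power does not fall, because M only reduces residual variance.

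Simulation with 4,000 trials per cell, 140 per group, agreed for the first two rows: mean estimates 8.81, 6.18 and 3.78 mm (power 66%, 44%, 28%), and 10.56, 9.42 and 8.12 mm (83%, 80%, 84%).

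**4. Limits of the check.** The model contains only treatment and M. With baseline VAS, age, sex and baseline severity also included, the residual SD and the relevant partial correlation would differ. The table shows how sensitive the coefficient is; it does not predict this trial's result. The auricular points and adverse events are also post-randomisation but were not quantified.

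**The case against.** The phrase is loose, and harmless meanings are open. It could mean the T0 Lattinen score, or other findings at entry: Results measures describes a clinical history and pain duration taken at the initial evaluation, and the separate severity item covers only intensity and frequency. It could also be a clumsy reference to the professional as a factor, since randomisation is stratified by therapist and one secondary objective compares effectiveness by the professionals' training. The analysis section does not name the Lattinen test in this connection. All of this stands. A reader might infer that the plan deliberately adjusts for an on-treatment pain score, and the text does not establish that. Nor does it exclude it: the words refer to recorded results, set no time limit, and are listed as terms that go into the model.

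A reader might also infer that the trial's primary analysis is biased and that the stated 90% power is lost. The document does not support this. It plans an unadjusted comparison, which the sample-size calculation matches and which no regression covariate can affect, and it calls the adjustment for imbalance secondary. On the other side, the analysis section mentions ITT only for this regression, and the Discussion bases the main outcome on ITT. Which analysis is primary is therefore not settled either way.

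Finally, attenuation depends on treatment moving the Lattinen score. That is plausible, because the trial makes it an outcome, but it is an assumption.

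**Conclusion.** The point holds as a defect in the stated covariate list. Followed as written, the sentence admits post-randomisation outcomes, scored by an unblinded therapist, into a regression labelled ITT, and the resulting coefficient would not estimate the ITT effect. If treatment improves the Lattinen score, and that score correlates positively with the VAS within arms, the coefficient is too small. Over the assumed correlations of 0.3 to 0.7 and a half to full standardised shift, it would lie between 10.6 and 3.75 mm instead of 12.5 mm, with the adjusted model's power between about 84% and 27%. With no shift there is no bias.

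The conclusion reaches only the adjusted model. Even if that model is supportive, it could contradict the unadjusted result for no reason other than its covariates.

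**What to change.** In the Statistical analysis section, delete the reference to therapist-recorded results. State that the regression may include only variables measured before randomisation (baseline VAS, T0 Lattinen items or baseline severity, age and sex) plus the therapist stratification factor. Analyse post-baseline Lattinen scores only as outcomes, or use them as auxiliary variables if missing VAS values are imputed. If the phrase was meant as the therapist's identity or the T0 Lattinen score, write that instead. In the same edit, say whether the unadjusted comparison or the regression is primary.

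The cost is a sentence or two of text. No new data are needed, and the sample size is unaffected.
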